#### Primary implementation outcome: ownership of action plans at 12 months

The primary implementation outcome is the proportion of patients with an action plan. We will measure action plan ownership by a quality improvement questionnaire mailed to 50 patients randomly selected from the clinically eligible population in 32 randomly selected practices (16 practices in each trial arm). Ownership of an action plan is defined as the proportion of people (≥ 5 years of age) who respond ‘Yes’ to the question ‘Has your asthma nurse or doctor provided you with an asthma “action plan”?’ in the OPC quality improvement questionnaire mailed at 12 months. The questionnaire will be mailed, with one reminder sent by SMS.

#### Secondary outcomes

Table 2 displays the secondary outcomes that will be assessed from routine data at baseline, 12 months and 24 months extracted by OPC under their service-level agreement with practices.

**Table 2 Tab2:** Secondary outcomes

Secondary outcomes	Description
Asthma symptom control	We will assess asthma control using coded data for the Royal College of Physicians 3 Questions (RCP3Qs) [60]. Status with regard to these three questions is routinely recorded (in England) for the QoF. The clinical implications of the responses have been established [61]
Asthma attacks	We will report: • Unscheduled care in the first year post-randomisation as a secondary outcome (unscheduled care in the second year post-randomisation is the primary outcome) • The proportion of people prescribed a course of oral steroids in the previous 12 months (a recognised marker of a severe attack [62]), and the number of steroid courses/patient/year
GINA control	We will assess the composite outcome of ‘GINA control’. The GINA guidelines define control over a period of 4 weeks as no night-time symptoms or activity limitation, symptoms/requirement for rescue medication < 2 doses/week and no attacks in previous year [4]. We will assess this: • For the whole population from routine data (e.g. from responses to the RCP 3Qs, prescribing data), • For the randomly selected sub-group from the responses in the quality improvement questionnaire that enable assessment of GINA control
Prescribing outcomes	We will measure: • The proportion of people prescribed inhaled steroids and number of prescriptions/year; • The proportion of people prescribed reliever medication and number of prescriptions/year; • The proportion of people using a sub-optimal treatment regimen (defined as a ratio of the number of prescriptions for controller medication to total number of prescriptions for all asthma medication < 0.5 [63]
Asthma management	• Asthma reviews will be measured using the proportion of people with active asthma reviewed each year • Provision of action plans (as opposed to ownership which will be assessed in the quality improvement questionnaire) will be measured by assessing the proportion of people (≥ 5 years) who have a record of the provision/updating of an action plan in the previous 3 years assessed at 12 and 24 months post-randomisation
Confidence in self-management and professional support	The Asthma Bother Profile (management section) reflects quality of asthma care and patient’s confidence in ability to self-manage on a scale of 0 (no confidence) to 5 [64]. These questions will be included in the quality improvement questionnaire

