## Abstract

**Background:**

Asthma is a common long-term condition and major public health problem. Supported self-management for asthma that includes a written personalised asthma action plan, supported by regular professional review, reduces unscheduled consultations and improves asthma outcomes and quality of life. However, despite unequivocal inter/national guideline recommendations, supported self-management is poorly implemented in practice. The IMPlementing IMProved Asthma self-management as RouTine (IMP^2^ART) implementation strategy has been developed to address this challenge. The aim of this implementation trial is to determine whether facilitated delivery of the IMP^2^ART strategy increases the provision of asthma action plans and reduces unscheduled care in the context of routine UK primary care.

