For three decades [30], national and international guidelines have recommended—unequivocally—that people with asthma should be provided with self-management education, reinforced by a personalised action plan and supported by regular review with a healthcare professional [3–5]. Implementation, however, remains poor in routine clinical practice. Surveys from the UK, USA, Northern Europe and Australia reveal that less than a third of people with asthma have an action plan [31–34]. Routine primary care data from our developmental work revealed that only 6% had a record of being given an action plan [35]. In 2014, the UK National Review of Asthma Deaths highlighted that half the people who died had not accessed medical help, emphasising the vital importance of asthma self-management to facilitate timely response to deteriorating asthma control [36].

The solution will need a whole system approach [37]. An NIHR HS&DR-funded systematic review of the implementation of supported self-management concluded that whilst patient education, professional training and organisational support were all essential, they were rarely effective in isolation [38]. Effective implementation was multifaceted and multidisciplinary, engaging patients, training and motivating professionals, within the context of an organisation that actively supports self-management [39]. A systematic review of asthma implementation studies [39] identified small randomised controlled trials (RCTs) evaluating either patient education, professional training or organisational support and observational studies reporting whole system initiatives—including some very large effective national projects [40, 41]. There were no randomised trials evaluating whole system implementation strategies: a gap that the current study aims to address.

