	Professional content of the *Living with Asthma* website	A range of online resources for healthcare professionals (e.g. action plans, patient information for use in reviews) have been collated on the professional pages of the *Living with Asthma* website	Added information and resources related to providing remote asthma reviews [54, 55]
Organisation***	Asthma Review Template [56, 57]	An asthma review template that will be embedded in practice systems (EMIS, SystmOne, Vision, Microtest) for use in asthma reviews. Templates will be ‘QOF-compliant’ [47], patient-centred, highlight action plan provision, and link to the *Living with Asthma* website	No change
	**Audit and feedback **[58]	Annual audit reports focusing on supported self-management will be provided at baseline, 12 and 24 months. Brief monthly reports will be delivered to practices for the duration of their participation in the trial, focusing on a summary of unscheduled care, patients reviewed and action plan provision compared to an OPC database average. The email containing the monthly report will include a ‘top tip’. Reports allow data to be de-anonymised by the practices, so that ‘at-risk’ patients can be identified and invited for review	Annual audit and feedback report updated to include a section on COVID-19: number/% of patients considered at high risk of complications due to COVID-19; number/% of patients with confirmed or suspected COVID-19; patient COVID-19 vaccination status (number/%)

^*^Developed with Patient and Public Involvement (PPI) colleagues

^**^Developed with Education for Health (EfH)

^***^Developed with Optimum Patient Care (OPC)

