### Sample size for the implementation outcome of asthma plan ownership

About a third of people who responded to an Asthma and Lung UK survey in 2014 owned an action plan [68]. Assuming a 15% increase in asthma action plan ownership in the IMP^2^ART implementation arm, we would have an effect size of *h* = 0.322. To detect this difference with 90% power, 203 patients in each arm would be needed without clustering. Accounting for within general practice clustering with ICC = 0.03, we would need 20 completed questionnaires from 32 clusters (16 practices from each arm), a total of *n* = 640 patients. Given the average questionnaire response rate is ≈45%, we will post questionnaires to 50 participants/practice.

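### The secondary outcome called provision of action plans is a coded record, and only implementation practices get prompts that may increase coding, so a between-arm difference mixes better recording with more plans given

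*Protocol article*

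**What the plan says.** The Secondary outcomes section of the protocol article introduces Table 2 as listing "secondary outcomes that will be assessed from routine data at baseline, 12 months and 24 months extracted by OPC". Under asthma management, provision is scored as the proportion of people aged 5 or over "who have a record of the provision/updating of an action plan in the previous 3 years", at 12 and 24 months after randomisation. Table 2 separates provision from ownership, which is measured by questionnaire. It does not separate provision from the recording of provision.

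Table 1 gives implementation practices a review template embedded in the record system, described as "patient-centred, highlight action plan provision". They also get monthly reports covering "patients reviewed and action plan provision compared to an OPC database average". The Facilitation section adds that facilitators monitor those reports and help practices that are struggling. Under usual care, control practices receive no strategy component, only a standard annual report with action plan feedback near its end.

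On levels, the Background says that in routine data "only 6% had a record of being given an action plan", while surveys show that "less than a third of people with asthma have an action plan". The sample size section for ownership says: "About a third of people who responded to an Asthma and Lung UK survey in 2014 owned an action plan".

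The Abstract words the aim as whether the strategy "increases the provision of asthma action plans and reduces unscheduled care". The formal aims list, and the primary implementation outcome, name ownership.

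**The concern.** A coded record can change for two reasons: more plans are given, or more of the plans given are coded. The strategy can act on both, in one arm only. Because updating also counts, noting an existing, previously uncoded plan at a templated review turns the outcome positive without a new plan.

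The stated protections do not reach this point. Extraction, data handling and analysis are blinded, but the code is entered earlier, by practice staff who know their allocation. The Strengths and limitations section accepts coding discrepancies in general terms. Its statement that both groups are affected equally concerns the QOF change and the pandemic, not a prompt given to one arm.

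At stake is interpretation. Coded provision is the only action plan measure described for all practices and the only one at 24 months. The Abstract and the opening of the Discussion word the aim as provision. A gain in recording could therefore be reported as more plans given.

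**Working it through.** The protocol gives no sample size, power or error rate for coded provision, so there is no stated figure to reproduce. What follows shows what could happen under stated assumptions.

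**1. Implied share of plans coded.** Capture = recorded rate / ownership.
- Ownership one third: 0.06/0.333 = 18%.
- Ownership 25%: 0.06/0.25 = 24%. Ownership 20%: 0.06/0.20 = 30%.
- The look-back behind the 6% is not stated. If it was one year with no overlap between years, three years would give 18% recorded, and capture 0.18/0.333 = 54%.

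**2. Difference from recording alone.** Assume the same true ownership in both arms: difference = ownership × (implementation capture − control capture). With ownership one third and control capture 18% (6% recorded):

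| Implementation capture (assumed) | Recorded | Difference |
|---|---|---|
| 28% | 9.3% | 3.3 points |
| 38% | 12.7% | 6.7 points |
| 50% | 16.7% | 10.7 points |

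**3. Ceiling.** With complete coding in the implementation arm, the largest difference is ownership minus the recorded control rate. At one third owning, this is 27, 18, 8 or 3 points for control recording of 6%, 15%, 25% or 30%.

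**4. Would it reach significance?** The inputs are borrowed from the primary clinical outcome: 70 practices per arm, mean 200 patients, coefficient of variation 0.8, ICC 0.07.
- Design effect = 1 + [(1 + 0.8²) × 200 − 1] × 0.07 = 23.89. Effective n = 14,000/23.89 = 586 per arm.
- Probability of p < 0.05 = Φ(difference/SE − 1.96).
- 6% v 10%: SE = √[(0.06×0.94 + 0.10×0.90)/586] = 0.0158; Φ(2.53 − 1.96) = 72%.
- The same 4 points from 15% (SE 0.0219): 45%. From 25% (SE 0.0259): 34%.
- The 6.7-point row in step 2 (SE 0.0169): 98%.
- 6% v 10% with ICC 0.03 or 0.15 instead: 96% or 42%.

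**5. Can the questionnaire practices show it?** The plan is 16 practices × 20 completed questionnaires = 320 per arm. At 25% to one third owning, that is 80 to 107 people per arm answering Yes. Compare the share of them with a code:
- 18% v 40%, n = 80, ICC 0.07: design effect 1 + (5 − 1) × 0.07 = 1.28, SE 0.079, power 80%.
- 18% v 40%, n = 107, ICC 0.03: design effect 1 + (6.7 − 1) × 0.03 = 1.17, SE 0.065, power 92%.
- 24% v 40%, same two settings: 49% and 65%.

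**6. Could the all-practice result be corrected by arm-specific capture?** Take ownership 30%, so 96 Yes answers per arm, with capture 20% (0.06/0.30) v 40%. Half-width = 1.96 × 0.30 × √[0.8/(0.2×96) + 0.6/(0.4×96)] = 14 points, before clustering and error in specificity. Among the responders themselves, correcting the code by its own sensitivity and specificity simply returns the questionnaire proportion.

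**The case against.** **The outcome hierarchy already protects the main conclusion.** The primary implementation outcome is patient-reported ownership, which does not depend on coding, and the formal aims name it. This stands and limits the point to one secondary outcome. It does not cover the 24-month result, the practices outside the questionnaire sample, or the wording of the Abstract and Discussion.

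**A reader might infer that the code misses most plans.** The documents do not show this. The 6% and the one third come from different populations and methods, survey responders may over-represent owners, and the Background cites 6% as evidence of poor implementation, not of under-coding. With another look-back, capture could exceed half (step 1).

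**A reader might also infer that recording differs between arms by design.** That is too strong. Use of the template is optional, the text does not say that it changes coding of plans already given, and control practices get some annual feedback on action plans. Differential recording is plausible but not established.

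**The 6% may be out of date.** It comes from developmental work, and the QOF changed in late 2020, before recruitment began. Coding may have risen in English practices in both arms, which shrinks the possible artefact (steps 3 and 4). In addition, two of the three look-back years precede randomisation at the 12-month assessment, which dilutes any difference.

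**An extra table could be left to the analysis plan.** That is fair for the table. The name and definition of the outcome, and the one-sided prompts, are what the protocol itself fixes.

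**Conclusion.** The point holds in a limited form. As defined, the outcome measures recorded provision, and a between-arm difference may combine better recording with more plans given. The protocol states no safeguard aimed at coding that differs by arm.

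The size is unknown. Illustrative differences from recording alone run from about 3 to 11 points if control recording is 6%, ownership is one third in both arms, and capture rises to 28–50% in the implementation arm. Those capture values are assumptions without a source in the documents, and the ICC belongs to another outcome. With control recording of 15–25%, a 4-point artefact would reach significance about 34–45% of the time, not 72%. The figures therefore do not support saying that a positive result would be spurious, or that false significance is near certain.

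The primary clinical outcome and the primary implementation outcome are not affected by this point. It is a cheap improvement that changes what may be concluded from one secondary outcome.

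**What to change.** 1. Name and report the outcome as recorded provision.
2. In the 32 questionnaire practices, tabulate by arm the 12-month coded record against the questionnaire answer: the share of Yes responders with a code, and of No responders with a code. If patient-level linkage is not permitted (the routine data are anonymised and no linkage is described), compare coded and reported proportions at practice level by arm.
3. State with the table that the questionnaire item has no 3-year window, so an older plan can be reported without a qualifying code, and that response is expected to be about 45%.
4. State that a conclusion that more plans were provided rests on the questionnaire outcome, and read the all-practice and 24-month coded results in the light of the table.

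An all-practice estimate corrected for sensitivity and specificity is not worth adding, because it is too imprecise to help (step 6 of the working).

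The cost is one extra table from data the trial already plans to collect through the same provider, and a more cautious conclusion for this outcome. The table would probably reveal a capture gap as wide as 18% v 40% but could miss a smaller one, so the absence of a visible gap would not prove equal recording.

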### Sample size calculations

Sample size for primary clinical outcome of unscheduled care within the previous year.

In our preliminary work, we found an unscheduled care rate of 34% [35]. We chose an absolute difference of 7% (from 34 to 27%) between trial arms as being the minimum important effect clinically and to health services. This is approximately half the effect achieved in effectiveness trials of supported self-management [6]. To detect this difference with 90% power and 5% significance level, 1868 patients would be required in an individually randomised trial without clustering.

Assuming an intraclass correlation (ICC) of 0.07 (taken from experience of pragmatic implementation studies, and supported by our analysis of data from 379 OPC practices) and assuming 200 individuals/practice, we need 70 practices (14,000 patients) in each group (increased to 72 practices/arm to allow for practice withdrawal) to detect the minimum important effect with 90% power and 5% significance level. Patients will only be included in the analysis dataset if they have ‘active asthma’ with the same practice at baseline, 12 months and 24 months follow-up, which avoids individual patient attrition. We originally intended to limit recruitment to practices with a list size > 6000 (assuming 6% will have active asthma [65]) to avoid cluster sizes < 200 (and randomly sampling if clusters were > 200). During recruitment, it became clear that this excluded many small rural general practices in Scotland, so we opted to allow variable cluster sizes (including a few clusters likely to be < 200). Furthermore, the COVID-19 pandemic resulted in a reduction in asthma attacks [66, 67], and an analysis of the OPC dataset (*n* = 286 practices) in September 2021 showed that 25.8% was a more realistic estimate of the proportion with unscheduled care that we could expect in the control group. Maintaining the recruitment target of 144 practices (140 after loss to follow-up) and allowing for a variable cluster size (mean = 200; coefficient of cluster size variation = 0.8), the study would have 94.7% power to detect a reduction from 25.8 to 18.8%.

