**Fig. 1 Fig1:**
[figure not shown]
SPIRIT figure of enrollment, interventions and assessments

To be eligible, practices must use one of the four common electronic health record (EHR) systems (EMIS, SystmOne, Vision or Microtest) for which components of our implementation strategy have been designed, and agree to Optimum Patient Care (OPC: a social enterprise that leads quality improvement initiatives involving routine data extraction from practices https://optimumpatientcare.org) extracting anonymised routine coded data to measure the primary and other outcomes of the study. A successful extraction of data is a requirement to (a) demonstrate that there are no insurmountable governance or technical problems, (b) establish that the practice data would allow assessment of the primary health outcome, and (c) for use in the baseline audit and feedback reports.

Practices will be of varying sizes (to reflect the range of UK primary care) and thus have different numbers of ‘active asthma’ patients. Active asthma is defined by the UK Quality and Outcome Framework (an annual reward and incentive programme for all general practices in England) as having a coded diagnosis of asthma and having been prescribed an asthma medication within the previous year [47]. Our sample size calculation takes variable cluster size into consideration, but we will exclude very small practices likely to have substantially fewer than 200 patients with ‘active asthma’ registered throughout the trial. (Note: this will be an estimate at the time of recruitment as we will not know the exact cluster sizes until the final routine data are available at the end of the trial). Finally, we will exclude practices undertaking research or initiatives that might affect our outcomes, and practices that work closely with another participating practice (e.g. as part of a network or federation). Decisions about potential contamination will be overseen by a sub-committee (chaired by [name]).

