### Randomisation

The unit of randomisation will be the general practice. Remote online randomisation (1:1 implementation:control) will be provided by the Pragmatic Clinical Trials Unit (PCTU), Queen Mary University of London. Stratifiers, determined according to contextual influences identified during developmental work [50, 51], will be deprivation status (less deprived, ≤ median deprivation score/more deprived, > median deprivation score), practice list size (small, ≤ 8035 patients; large, > 8035 patients) and GP training status of the practice (yes/no). In a second step, 32 practices will be randomly selected for quality improvement questionnaire data collection, ensuring that these practices are distributed evenly between the implementation and control groups. Randomisation is implemented in REDCap (Research Electronic Data Capture) software [69] and allocations will be requested by the programme manager (VH).

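### The planning cluster sizes (mean 200, CV 0.8) do not fit the practices the protocol says it will recruit, and at those inputs the planned analysis has about 82% power, not 94.7%

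*Protocol article*

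**What the plan says.** All references are to the protocol article.

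- **Practice eligibility criteria and recruitment:** "we will exclude very small practices likely to have substantially fewer than 200 patients with" active asthma registered throughout the trial. This is described as an estimate made at recruitment, since exact cluster sizes are known only at the end.
- **Sample size calculations, first design:** a 7-point difference from 34% to 27%, a fixed 200 patients per practice and 70 practices per arm (72 with withdrawals). "Assuming an intraclass correlation (ICC) of 0.07" is the only ICC given for this outcome. Recruitment was to be limited to lists above 6000, with larger clusters sampled down to 200.
- **Sample size calculations, revised design:** the list-size limit was dropped because it excluded many small rural Scottish practices. Cluster sizes may now vary, "including a few clusters likely to be < 200". Power is restated as 94.7% for 25.8% versus 18.8% with 140 practices, "allowing for a variable cluster size (mean = 200; coefficient of cluster size variation = 0.8").
- **Randomisation:** list size is a stratifier, "small, ≤ 8035 patients; large, > 8035 patients".
- **Statistical analysis:** the primary analysis is an unweighted independence estimating equation on participant-level data with robust standard errors.

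**The concern.** A mean of 200 with a CV of 0.8 means an SD of 160. For the mean to be 200 while sizes vary that much, many practices must lie well below 200, or a very few must be enormous. Neither matches a recruitment rule that screens out practices substantially below 200 and expects only a few below it.

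The likely explanation is that 200 was the fixed cluster size when larger practices were to be sampled down. It then stayed as the mean after that sampling was abandoned.

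What is at stake is the power statement. An unweighted participant-level analysis loses efficiency quickly as the CV rises, so whether the trial sits near 82% or above 90% depends on an input that does not describe the intended practices.

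**Working it through.** **Inputs.** ICC 0.07, m = 200, CV = 0.8, 70 practices per arm, 25.8% versus 18.8% (Sample size calculations). A two-sided 5% test is assumed, because sidedness is not stated. Prevalence of active asthma is 6% (same section). Yearly register turnover is 20%, from one practice (Primary clinical outcome).

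**1. First design.** The equal-cluster design effect is 1 + 199 × 0.07 = 14.93. Then 1868 × 14.93 / 400 = 69.7, so 70 practices per arm. This reproduces.

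**2. The stated 94.7%.** Use the relative-efficiency formula for an optimally weighted (mixed-model) analysis:

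- L = m·ICC / (m·ICC + 1 − ICC) = 14 / 14.93 = 0.938
- DE = 14.93 / (1 − CV²·L·(1 − L)) = 15.51
- Effective n per arm = 14,000 / 15.51 = 903
- Power (normal approximation, two proportions) = 94.7%. This reproduces.

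**3. The planned analysis at the same inputs.** For an unweighted independence analysis:

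- DE = 1 + [(1 + CV²)·m − 1]·ICC = 1 + (328 − 1) × 0.07 = 23.89
- Effective n per arm = 14,000 / 23.89 = 586
- Power = 82.2%

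**4. What mean 200 and CV 0.8 imply for practice sizes** (shape assumed):

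| Size below | Gamma | Lognormal | Of 140 practices |
|---|---|---|---|
| 200 | 60.6% | 63.7% | 85–89 |
| 100 | 31.0% | 26.3% | 37–43 |

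**5. A check that needs no shape.** Suppose 10% of practices are below 200 and none is below 100. The average shortfall over all practices is then at most 0.10 × 100 = 10, and the average excess above 200 must equal it. The variance is 160² = 25,600, of which the shortfalls supply at most 0.10 × 100² = 1,000. The remaining 24,600 must come from the excesses, so the largest excess is at least 24,600 / 10 = 2,460. At least one practice would therefore need about 2,660 retained patients. At 6% prevalence and two years of 20% turnover, that is a list of 2,660 / (0.06 × 0.64), or about 69,000.

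**6. Where the protocol's own figures point.** A list of 6000 gives 6000 × 0.06 = 360 patients, and 360 × 0.64 = 230 after two years. A list of 8035 gives 482, and about 309 after two years. Both are before clinical exclusions, for which no rate is given. On these figures 200 lies near the bottom of the first design's range, not at its centre.

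**7. Sensitivity of power to the inputs** (ICC 0.07, 70 per arm; the replacement values are illustrative):

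| Mean | CV | Unweighted (planned) | Optimally weighted |
|---|---|---|---|
| 200 | 0.8 | 82.2% | 94.7% |
| 300 | 0.8 | 82.7% | 95.3% |
| 200 | 0.5 | 90.7% | 95.2% |
| 300 | 0.5 | 91.2% | 95.6% |
| 300 | 0.4 | 93.0% | 95.7% |
| 200 | 0.3 | 93.9% | 95.3% |
| 300 | 0.3 | 94.3% | 95.7% |

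For the planned analysis the mean hardly matters and the CV matters a great deal. Cutting the gamma or lognormal distribution off below 150, as one reading of the size rule, gives a mean of 297–309, a CV of 0.48–0.57 and unweighted power of about 90–91%.

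**The case against.** **The size rule is soft.** A reader might infer that the eligibility rule sets a floor of 200 and so forbids the planning distribution. The text does not go that far. It excludes only practices likely to be substantially below 200, it calls this an estimate, and it admits some smaller clusters. A very skewed set can also meet the figures arithmetically, for example 91% of practices at 150 and 9% at about 712. This objection stands against the word forbids. It does not remove the misfit, because that set puts nine in ten practices below 200, which is not a few.

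**The inputs are probably cautious.** A reader might infer that the trial is underpowered. If the size rule is followed, the mean is probably larger and the CV smaller, and both raise power. Under the formula behind 94.7%, the correction is worth only about one point. This stands: the misfit in the inputs does not by itself run in the harmful direction.

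**The 82% arises from the formula, not from the cluster sizes.** That is correct. It comes from pairing the printed inputs with the planned analysis. It belongs here because the choice of analysis is what makes the CV matter. A smaller ICC could also bring the unweighted figure up (about 94.5% at 0.045), but the protocol gives only 0.07 for this outcome.

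**The replacement mean is not known.** A reader might take 309, or something a little lower after exclusions, as the true mean and scale up the patient total accordingly. The protocol does not support this. It does not say that 8035 is a typical list size, the turnover comes from one practice, and no exclusion rate is given.

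**Conclusion.** The point holds. The printed mean and CV do not describe the practices that the eligibility section and the sample size section say will be recruited. About 61–64% of practices would lie below 200 and 26–31% below 100 under a gamma or lognormal shape. The shape-free check shows that the misfit is not an artefact of that choice.

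At the printed inputs the planned unweighted analysis has about 82% power. That is below the 90% for which the trial was first sized and about 12 points below the stated 94.7%. The figure assumes an ICC of 0.07, 70 analysed practices per arm, a two-sided 5% test and no gain from covariates. With illustrative CVs of 0.3–0.5 it would be about 91–94%, so the trial may well be adequately powered. The document does not allow the true mean or CV to be derived, and the finding is not that the trial is too small.

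**What to change.** In the sample size section:

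1. Replace the mean and CV with values from the baseline extractions of recruited practices, allowing for expected two-year retention and clinical exclusions. A successful extraction is already an eligibility requirement, so the data should exist.
2. Restate the expected number of patients and the power from those values, using the design effect for the unweighted independence analysis.
3. If a mean of 200 and a CV of 0.8 are kept, state power of about 82% in place of 94.7%.
4. Reconcile the eligibility wording and the expectation of a few clusters below 200 with whichever distribution is used. If practices well below 200 are being admitted, say so.

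The cost is a short recalculation and some revised sentences, with no change to recruitment or design. The downside is that the stated power may look less favourable.
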